## Abstract

**Background:**

Screening with prostate-specific antigen (PSA) test for prostate cancer is considered a preference sensitive decision; meaning it does not only depend on what is best from a medical point of view, but also from a patient value standpoint. Decision aids are evidence-based tools which are shown to help people feel clearer about their values; therefore it has been advocated that decision aids should contain a specific values clarification method (VCM). VCMs may be either implicit or explicit, but the evidence concerning the best method is scarce. We aim to compare the perceived clarity of personal values in men considering PSA screening using decision aids with no VCM versus an implicit VCM versus an explicit VCM.

**Methods:**

Male factory employees from an industrial facility in the Northern region of Portugal aged 50 to 69 years old will be randomly assigned to one of three decision aid groups used to support prostate cancer screening decisions: (i) decision aid with information only (control), (ii) decision aid with information plus an implicit VCM, (iii) decision aid with information plus an explicit VCM.

Men will be allowed release time from work to attend a session at their workplace. After a brief oral presentation, those willing to participate in the study will fill the baseline questionnaire, plus a 5 point-Likert scale question about intentions to undergo screening, and will then receive the intervention materials to complete.

We estimated a total sample size of 276 participants; with 92 in each group.

The primary outcome will be the perceived clarity of personal values assessed by the Portuguese validated translation of the three subscales of the Decisional Conflict Scale. Secondary outcomes will be intention to be screened (before and after the intervention), the total score from the Decisional Conflict Scale and the self-report of having or not undergone screening at 6 months.

**Discussion:**

This study will add to the body of evidence on the role of decision aids to support health preference-sensitive choices and provide further insight on the impact of different methods for eliciting people’s values embedded within a decision aid.

**Trial registration:**

NCT03988673 - clinicalTrials.gov (2019/06/17).

## Background

Prostate cancer is a leading cause of men cancer worldwide [1]. Nevertheless, screening for prostate cancer using a prostate specific antigen (PSA) test remains a controversial issue; implying a trade-off between benefits (mortality reduction, early diagnosis) and risks (high instances of overdiagnosis and overtreatment in conjunction with the consequent side effects, as well as false positive and false negative test results) [2, 3]. Thus, the PSA test used to screen for prostate cancer is considered a preference sensitive decision; meaning it does not only depend on what is best from a medical point of view, but also taking into account patient preferences; i.e., the values a patient attaches to the advantages and disadvantages of that option [4].

According to the International Patient Decision Aids Standards (IPDAS) Collaboration, decision aids are evidence-based tools designed to help people participate in decision making about health care options with the aim of improving the quality of the decision [5]. The most recent systematic review concluded that decision aids could increase patient knowledge about screening, make people feel clearer about their values, reduce decisional conflict, and promote an active patient role in decision making [6].

In consideration of evidence on the role of decision aids in helping to clarify patient values, the IPDAS suggested that decision aids should include some values clarification methods (VCMs) [7]. VCMs are defined as strategies designed to help patients evaluate the desirability and attributes of different options in order to identify the option they prefer [8]. The methods used for values clarification are often classified as being either implicit or explicit [9]. With implicit techniques, patients are presented the pros and cons of the available options, on a balance sheet, for instance, and are expected to weigh up the desirability of the different options on their own and, ultimately, they will develop a preference for one of the options [10]. On the other hand, explicit VCMs are designed to engage the patient in tasks to specifically compare the relative importance of characteristics relevant to a decision [11]. Examples of such explicit methods are rating and ranking tasks as well as social matching which consists of viewing others engaged in decision making and identifying one’s own values to the values of these individuals [12].

In a previous version of the Cochrane review of patient decision aids, 59.1% of the decision aids considered included explicit methods used to clarify values. Decision aids with explicit VCMs resulted in a higher proportion of patients choosing a screening option congruent with their values (RR = 1.51; 95% CI 1.17 to1.96; *n* = 13) in comparison to a simple decision aid without explicit values clarification or usual care [13]. Implicit VCMs were not assessed in this review.

Nevertheless, there is still scarce evidence concerning whether implicit and explicit values clarification methods may make a difference on patient reported values and preferences compared to instance where no VCMs are used.

While engaging in an explicit values clarification task, the patient may gain insight into the value he/she assigns to each option, which could help him/her to select a preferred option and to be able to communicate his/her preferences to others [10]. According to this rationale, values clarification methods may be more helpful when, in addition to helping users to realise what matters to them, they clarify how what matters to them determines which option may be the preferred one [14]. On the other hand, explicitly exploring the pros and cons of each option may increase uncertainty towards the choice and, thus, implicit VCMs may be superior [9].

### Objectives

To compare the perceived clarity of personal values in men considering PSA screening using decision aids with no VCMs versus an implicit VCM versus an explicit VCM.

### Trial design

Parallel three group (1:1:1) randomized controlled trial.

## Methods

50 to 69-year-old male factory workers will be randomly assigned to one of three decision aid groups supporting prostate cancer screening decisions: (i) decision aid with information only (Control), (ii) decision aid with information plus an implicit VCM, and (iii) decision aid with information plus an explicit VCM. Figs 1 and 2 and Table 1 summarize the main trial steps.

**Fig. 1 Fig1:**
[figure not shown]
Randomisation of trial participants

**Fig. 2 Fig2:**
[figure not shown]
Sequence of main trial steps

**Table 1 Tab1:** Schedule of enrolment, interventions, and assessments

	STUDY PERIOD					
	Enrolment	Allocation	Post-allocation			Close-out
**TIMEPOINT****	***-t***_***1***_ **2 weeks before**	**0** **session**	***t***_***1***_ **session**	***t***_***2***_ **session**	***t***_***3***_ **session**	***t***_***4***_ **6 months later**
**ENROLMENT:**						
**Eligibility screen**	X					
**Informed consent**	X					
**Allocation**		X				
**INTERVENTIONS:**						
***[Decision aid without VCM]***				X		
***[Decision aid with implicit VCM]***				X		
***[Decision aid with explicit VCM]***				X		
**ASSESSMENTS:**						
***[baseline variables]***			X			
***[Screening intention]***			X		X	
***[Decisional conflict scale]***					X	
***[Self-reported PSA screening]***						X

### Study setting

The trial will be held at an industrial facility in the Northern region of Portugal.

### Eligibility criteria

To participate in the study, men should be aged 50 to 69 years, be at average risk for prostate cancer (e.g., no personal or family history of prostate cancer; thus, not at high risk), and be able to provide written informed consent. Those unable to understand written Portuguese will be excluded. The baseline questionnaire will assess the participants’ eligibility.

### Interventions

“Making the best choice” is an English language prostate cancer printed screening decision aid which has been rigorously developed [15] and extensively tested [16–19] by a workgroup from Georgetown University (United States of America). We were given permission to translate and adapt the decision aid to the Portuguese population. The decision aid includes different sections: introduction to prostate and prostate cancer; screening tests (results, benefits and risks); treatment (options, benefits and risks); prostate cancer risk factors; encouragement to share decision-making with a physician; a values clarification method; and resources to access additional information (references and a glossary). KT, who was the principal investigator of the original decision aid is a co-investigator in this project. The results from the translation and cultural adaptation of the decision aid to the Portuguese population were recently published [20]. The testimonials section of the decision aid will be excluded in this study since this can be considered a type of values clarification method and could thus bias the results.

The VCM in the decision aid was adapted from a previous study [21] and is composed of 10 statements addressing the most important aspects involved in prostate cancer screening decisions. The control group will receive the decision aid without any VCMs. One intervention group will receive the decision aid with the implicit VCM. In this version of the decision aid, men will be presented with 10 statements. For the first set of five statements, participants will be informed that “Men who have made these statements often decide to get screened” and for the second set of five statements, they will be informed that “Men who have made these statements often decide NOT to get screened.” The other intervention group will receive the decision aid with an explicit VCM. For each of the 10 statements, men will be asked whether each sentence sounds like him or not.

Men will be asked their personal position towards screening before and after reading the decision aid.

### Outcomes

The primary outcome will be the perceived clarity of personal values assessed by the Portuguese validated translation of the three subscales of the Decisional Conflict Scale (DCS) [22]. The Values Clarity subscores range from 0 (feels extremely clear about personal values for benefits and risks/side effects) to 100 (feels extremely unclear about personal values); lower scores suggest better clarity.

Secondary outcomes will be intention to be screened and the total score from DCS. Respondents will be asked a single question about their intention to undergo a PSA screening, using a 5 point-Likert scale (ranging from “strongly disagree” to “strongly agree”; intention to undergo PSA screening will be considered positive if the respondent replies with “agree” or “strongly agree”). Total scores from the 16-questions DCS (including the subscales values clarity, informed decision making, effective decision making, decision making support, decision making uncertainty) range from 0 (no decisional conflict) to 100 (extremely high decisional conflict), discriminating between those who make and delay decisions [23]. Furthermore, prostate cancer screening status at 6 months after the intervention will be assessed by way of a self-report.

### Patient timeline

After a brief oral presentation session, men willing to participate in the study will be invited to stay and fill the baseline questionnaire plus a 5 point-Likert scale question about intention to undergo screening. These will have the same numeric code as the sealed envelopes containing the materials to be distributed. Participants should then complete the required questions after intervention assignment during the same session.

### Sample size

We estimated a total sample size of 276 participants, 92 in each group, using the ANOVA test for three groups and considering an average effect size of 0.2 with a significance level of 0.05 and 80% power, attending to the psychometric properties of the DCS and also accounting for 10% of participants leaving the study before conclusion.

### Recruitment

Two weeks in advance, male employees will be sent an invitation letter to participate in a facultative session about prostate cancer screening and presenting the trial and how to participate. The session will be held at their workplace, during business hours, and will be presented by the lead investigator. During the session, men will be invited to stay after the initial presentation if they are willing to participate in the trial. They will then be presented with written information about the project, the lead investigator will be available to answer any questions and the willing participants will be asked to give their written consent. Men will be allowed release-time from work to participate in the session.

### Blinding

Due to the nature of the intervention, it will be impossible to fully blind participants. In order to minimize bias, participants will know that different formats of the decision aid will be assessed, but they will not be informed about the differences in formats or about the research hypotheses. After the decision aid packages are given to participants, the lead investigator will no longer interact with participants; thus, she will not be aware of which decision aid has been allocated to individual participants. Data collection forms will be collected by other members of the research team. Since the main outcome is self-reported, it is impossible to blind outcome assessors; however, data collection procedures will be the same, regardless of the allocated group. The statistician assessing the data and the first author will not be blinded to allocation when analyzing or drafting the manuscript, respectively.

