### Data management

Participant paper files, only identifiable by a participant ID number, will be stored in numerical order in a secure place at the University of Porto. Participant paper files will be maintained in storage for a period of 3 years after completion of the study. All anonymized data will be entered electronically and, only after all data has been entered, will researchers contact the statistician who prepared the randomization schedule to know which group was assigned to individual participants access to the study data will be restricted to the research team based at University of Porto. A data tracking system with time stamps will be implemented for audit purposes. A password system will be utilized to control access to de-identified electronic data and these passwords will be changed every 3 months.

To ensure that we can follow participants for screening participation after 12 months, we will keep a single file which links participant ID number to participant name, phone number and one next of kin phone number. This electronic file will be kept by a team researcher not based at the University of Porto.

Anonymized data will be analyzed on a personal computer belonging to one of the authors based at the University of Porto.

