### Statistical methods

After collection, data will be analyzed using Microsoft Excel 2016® and SPSS Statistics 25.0®. Participants will be analyzed in the group they were randomized to, regardless of actual intervention received. In order to analyze between group differences concerning perceived clarity of personal values, we will use One-way ANOVA (if the variable distribution is normal) or Kruskal-Wallis (if the variables are not distributed normally). Normal distribution of variables will be assessed by observing the respective histograms and validated with the Kolmogorov-Smirnov test. For continuous variables with normal distributions, data will be described using mean (M), standard deviation (SD), minimum (min), and maximum (max). For continuous variables not distributed normally, data will be described using median (Med) and the respective interquartile range [Q_1_; Q_3_]; Q_1_ being the first quartile and Q_3_ being the third quartile.

If either the ANOVA or Kruskal-Wallis tests demonstrates significant differences between groups, multiple comparisons will be conducted between groups pairs in order to detect between which groups there are differences.

To test independence between categorical variables, we will use Chi-square test for independence. Categorical variables will be described using absolute and relative frequencies, N (%). *p*-values ≤0.05 will be considered significant.

DCS total score is composed of 16 items (each one with a 5-point Likert response scale) divided in five subscores: uncertainty subscore (3 items), informed subscore (3 items), values clarity subscore (3 items), support subscore (3 items), effective decision subscore (4 items). For each participant partial scores and a total score will be calculated. Concerning missing values, those participants who do not answer at least 50% of the items of each subscale will be excluded from the analysis. The total score will be presented on a 0–100 scale [23].

If there are baseline differences between groups, we will perform multivariate analysis using linear multiple regression.

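### The analysing statistician is unblinded, with no reason given, while the test, adjustment and pairwise method are still open; masked codes plus a lock before group comparison would reduce this risk cheaply

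*Protocol article*

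**What the plan says.** **Who is blinded.** The Blinding section of the protocol article states: "The statistician assessing the data and the first author will not be blinded to allocation when analyzing or drafting the manuscript, respectively". The same section explains why participants cannot be fully blinded (the nature of the materials) and why outcome assessors cannot be (self-report). It gives no reason for the analyst.

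**Who holds the key, and until when.** Under the section on assignment and sequence generation, a statistician with no other role in the trial makes the schedule and prepares the envelopes. Under Data management, "only after all data has been entered, will researchers contact the statistician who prepared the randomization schedule to know which group was assigned". What is released is each man's actual group; no coded step comes in between.

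**What is still open at that moment.** Statistical methods sets these rules:

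- Primary test: "we will use One-way ANOVA (if the variable distribution is normal) or Kruskal-Wallis (if the variables are not distributed normally"; the choice rests on this: "Normal distribution of variables will be assessed by observing the respective histograms and validated with the Kolmogorov-Smirnov test".
- Adjustment: "If there are baseline differences between groups, we will perform multivariate analysis using linear multiple regression".
- Pairwise step after a significant omnibus test: "multiple comparisons will be conducted between groups pairs in order to detect between which groups there are differences". No method is named.

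**The concern.** The primary outcome is a subjective self-report and participants are only partly blinded, so the analysis is the stage at which blinding is easiest to keep. The protocol gives it up there, at the point where several decisions that affect the result remain to be made. An analyst who knows which arm is which can see whether calling a baseline imbalance worth adjusting for, or preferring one test or pairwise method, helps or hurts a given arm. The Background sets out a rationale for explicit methods and another for implicit ones, so a result in either direction would have a ready explanation.

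The credibility of the arm contrasts is at stake, above all implicit versus explicit, which is settled in the pairwise step. No design figure is affected.

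**Working it through.** **1. Do the stated reasons cover the analyst?** The two reasons concern men who see their own booklet and men who rate their own values. The analyst works from numbered records whose link to the arms is held by someone outside the trial. Neither reason carries over.

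**2. What does the existing safeguard protect?**

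| Stage | Allocation known to the researchers? | Source |
|---|---|---|
| Handing out envelopes | No (opaque, sealed) | Assignment and sequence generation |
| Data entry | Withheld | Data management |
| Choice of test, adjustment, pairwise method | Yes | Blinding; Data management |
| Drafting | Yes | Blinding |

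The safeguard is real, but it ends where the analysis begins.

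**3. How many routes to a primary p-value?** Three are named at most: ANOVA, Kruskal-Wallis and adjusted linear regression.

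**4. What can masking do?** The ANOVA F and the Kruskal-Wallis statistic do not change when the three group labels are permuted. Codes A/B/C therefore leave every omnibus p-value visible and unchanged. They hide which arm a choice favours. Masking removes selection by direction; stopping selection by size of p needs the choices to be made before outcomes are compared between groups.

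**5. Design figures, reproduced.** Inputs from Sample size: three groups, effect size 0.2 (read as Cohen's f, an assumption because the index is not named), alpha 0.05, power 80%, dropout 10%.

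- Noncentrality = N × f². With 82 per group: 246 × 0.04 = 9.84, power 0.804. With 81 per group: 243 × 0.04 = 9.72, power 0.798. So 82 per group are needed.
- Dropout: 82 / (1 − 0.10) = 91.1, rounded up to 92; 3 × 92 = 276, the stated total.
- None of these inputs depends on who knows the labels, so masking leaves both N and power as they are.

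**6. Illustrative size of the analytic freedom.** Simulation under the null: 10,000 runs, 82 per group, one baseline covariate with latent correlation 0.4 (assumed), rejection at p ≤ 0.05.

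| Strategy | Skewed three-item score | Normal score |
|---|---|---|
| ANOVA, fixed | 4.80% | 4.73% |
| Kruskal-Wallis, fixed | 4.72% | 4.73% |
| Adjusted regression, fixed | 4.98% | 4.77% |
| Smaller p of ANOVA and Kruskal-Wallis | 5.67% | 5.76% |
| Smallest p of all three | 7.38% | 7.32% |

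Monte Carlo standard error near 5%: √(0.05 × 0.95 / 10,000) = 0.0022, about 0.2 percentage points. The last two rows assume that the analyst always takes the smallest p-value. They bound the freedom under these inputs and do not predict what this analyst would do.

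**7. Can the test be chosen without group labels?** At the planned effect the between-group variance is f² = 0.04 of the within-group variance, or 0.04 / 1.04 = 3.8% of the total. The pooled distribution is then close in shape to the within-group one, so looking at it without labels is good enough for this purpose.

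**The case against.** The strongest reply is that the unblinding is openly disclosed, contradicts nothing else in the article and sits alongside real safeguards: outside generation of the schedule, forms collected by other team members with identical procedures across arms, allocation withheld until data entry is complete, and a time-stamped audit trail. The Background declares no favoured arm. The criterion for a baseline difference, the covariate list and the pairwise method may well stand in a full protocol or analysis plan that is not shown.

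Much of this stands. The exposure is confined to the analysis stage, no motive is shown, and the absence of those details from a journal article is no fault in itself. The planned unblinding, however, is a stated choice that an unseen plan would not undo.

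The reply also rightly blocks some stronger readings that a reader might infer:

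- *Exclusions for missing items are a matter of judgement.* They are not. The rule is a numeric 50% threshold: on a three-item subscale, 1.5 items, so at least two answers.
- *Normality is judged by eye alone.* The histograms are to be backed by a Kolmogorov-Smirnov test. The gap is only that nothing says what happens if the two disagree.
- *Crossing two tests with adjusted or unadjusted gives four primary p-values.* No adjusted Kruskal-Wallis is planned, and the article does not say that the regression replaces the primary test.
- *Unblinding raises the type I error to about 7%.* That figure comes from picking the smallest p-value, which masked codes alone would still permit. It measures the open choices, not the unblinding.

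**Conclusion.** The point holds as a low-cost improvement of minor to moderate weight. The article plans an unblinded analysis without a reason, discloses true allocation before analysis, and leaves the analyst some judgement over test, adjustment and pairwise method. Together these allow choices to be steered towards an arm. The bias is potential; nothing in the document shows that it would occur, and its size cannot be computed from what is given.

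The conclusion assumes that no unseen document fixes all three choices before disclosure. If one does, little exposure remains and the change would mainly add credibility. The simulation further rests on the assumed covariate correlation and on smallest-p selection.

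**What to change.** Amend Blinding and Data management so that disclosure comes in two steps, or state why masking the analyst is not feasible:

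1. Once data entry is complete, the outside statistician releases only codes A, B and C. The key to the codes stays with that statistician.
2. Arm-specific values clarification forms, if entered, stay in a separate file. Only the explicit arm answers the ten statements, so their presence would reveal that arm.
3. Before outcomes are compared between coded groups, the analyst fixes the test from the pooled outcome distribution, with a rule for disagreement between histogram and Kolmogorov-Smirnov test. Any covariates are fixed from baseline data, and the pairwise method is named.
4. Scoring, exclusions, models and outputs are run and locked under the codes, with a dated record.
5. The labels are then revealed for interpretation and drafting. Any later analysis is marked as such.

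Steps 1 and 2 deal with selection by direction; steps 3 and 4 with selection by p-value. The cost is a few sentences, one extra release step, one separate file if the forms are entered, and a short delay before interpretation. No staff are added, and the sample size and power stay as planned.
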